## Results

The primary outcome is the presence of depressive symptoms at 1-month follow-up. Several secondary outcomes will be measured, such as positive and negative mood, satisfaction with life, health-related quality of life, depressive rumination, and coping skills. In addition, satisfaction and acceptability of the intervention will be measured, such as the perceived helpfulness, satisfaction with use, and the depth of understanding of the content of SPARX. Dropout rates will be measured to study the feasibility of SPARX.

This study received funding from The Research Institute of Personalized Health Sciences, Health Sciences University of Hokkaido, and obtained institutional review board approval in September 2019. Data collection began in April 2019. Study enrollment is still ongoing. As of April 2019, 60 subjects have been recruited and baseline data were collected. Moreover, 24 subjects have already been allocated to the treatment group and have begun the intervention. We expect to complete the study by March 2020, followed by data analysis and submission of the final report by the end of 2020.

Irrespective of the results, the results of this trial will be published in a peer-reviewed journal and communicated through presentations at national and international conferences. Study participants will be informed about the trial results via a plain-language summary of the results that will be sent to them. Academic papers and summary reports will be provided to the funders.

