**Methods:**

In this 7-week, multicenter, stratified, parallel-group, superiority randomized trial, participants will be allocated to either a treatment condition (SPARX) or a wait-list control condition. SPARX is a fully automated program, which will be delivered to the mobile phone or tablet device of the participants. SPARX is designed as an interactive fantasy game to guide the user through seven modules that teach key CBT strategies. All participants will be recruited from universities via advertisements on online bulletin boards, the campus newspaper, and posters. Participants in the treatment condition will use the SPARX program weekly. The primary outcome is the reduction of depressive symptoms (using Patient Health Questionnaires-9) measured at baseline and weekly: once after the 7-week intervention and once at a 1-month follow-up. Secondary outcomes include satisfaction with the program and satisfaction with life, measured by the Satisfaction With Life Scale; positive and negative moods, measured by the Profile of Mood States Second Edition; social functioning, measured by the EuroQol Instrument; rumination, measured by the Ruminative Responses Scale; and coping, measured by the Brief Coping Orientation to Problem Experienced Inventory.

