## Methods

### Study Design

This is a multicenter trial and follows a stratified randomized, parallel-group superiority design. Participants will be randomized 1:1 to an intervention arm, which will consist of the game-based computerized CBT program SPARX or a wait-list control condition. Postintervention assessments will be carried out 7 weeks after baseline assessment. The participant flow through the trial is shown in Figure 1.

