### Sample Size

A meta-analysis of RCTs examining the effects of CBT in comparison to wait-list on depression in university students showed an effect size of 1.13 [34]. However, the effect sizes were smaller (0.56 [35] and 0.64 [36]) for studies in adults compared to those of internet-based and other computerized psychological treatments with wait lists. A meta-analysis of RCTs to examine the effectiveness of game-based digital interventions showed an overall effect size of 0.66 (against a wait-list control condition), 0.47 (with a target population of adolescent users), and 0.41 (type of game: psychoeducation and training, including the SPARX study) [22]. Additionally, a meta-analysis of RCTs to examine the effectiveness of technology-delivered interventions for depression and anxiety in children and adolescents showed an effect size of 0.45 compared to the wait-list group [37]. Considering these findings, we assumed a similar effect size (0.60) to that of internet-based and other computerized psychological treatments or game-based digital interventions against wait-list [22,35,36] for the reduction of primary outcomes assessed using Patient Health Questionnaire-9 (PHQ-9).

A power analysis showed that a target sample size of 90 was needed to detect an effect size of 0.60 with alpha=.05 and a power of 0.80 for a two-tailed test. Considering an anticipated 10% dropout [38], we will aim to recruit at least 100 (50 per group) participants to test the primary hypothesis of this study.

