### Measures

The primary outcome (Japanese version of PHQ-9) will be measured at baseline (T1), weekly throughout the interventions (T2-T7), at postassessment 1 week after the 7 intervention weeks (T8), and at 1-month follow-up (T9). Other assessments will be conducted at preassessment (T1), postassessment (T8), and 1-month follow-up (T9). Table 1 shows the schedule of assessments at various time points. At baseline (T1), demographics data will be collected, including gender, age, major in university, year of study, residence status; presence or absence of visits to psychiatric and counseling services; and presence or absence of the use of a gamified psychological program.

**Table 1 table1:** Overview of measurements.

Outcome	Scale	T1^a^	T2-T7^b^	T8^c^	T9^d^
Demographics	Developed by the authors	✓			
Depressive symptoms	PHQ-9^e^	✓	✓	✓	✓
Satisfaction with life	SWLS^f^	✓		✓	✓
Negative and positive moods	POMS-2^g^	✓		✓	✓
Social functions	EQ-5D^h^	✓		✓	✓
Rumination	RSS^i^	✓		✓	✓
Coping	Brief COPE^j^	✓		✓	✓
Stressor	DLSS^k^	✓		✓	✓
Satisfaction and acceptability	Developed by the authors				✓

^a^T1: baseline assessment (preassessment).

^b^T2-T7: assessment at each level.

^c^T8: assessment 1 week after the program.

^d^T9: assessment at 1-month follow-up.

^e^PHQ-9: Japanese version of Patient Health Questionnaire-9.

^f^SWLS: Satisfaction With Life Scale.

^g^POMS-2: Profile of Mood Scale, second edition.

^h^EQ-5D: Japanese EuroQol instrument.

^i^RSS: Japanese version of the Ruminative Responses Scale.

^j^Brief COPE: Brief Coping Orientation to Problem Experienced inventory.

^k^DLSS: Daily Life Stress Scale for undergraduates.

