#### Primary Outcome Measure

The primary outcome measure is the Japanese version of PHQ-9. The PHQ-9 is a self-reported questionnaire for assessing depressive symptoms of the preceding 2 weeks [39]. The questionnaire consists of nine items evaluated using a 4-point Likert scale to indicate the extent to which the participant agrees with the values expressed in each item (0, not at all; 3, nearly every day). Higher scores indicate more severe depressive symptoms. In an earlier study [39], this scale demonstrated good internal consistency (alpha=.93) and good convergent validity (correlation coefficient with the Kessler Psychological Distress Scale: *r*=.81) in a Japanese clinical population.

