### Statistical Analyses

The analysis for primary outcome measures will be conducted using a linear mixed model (LMM). The LMM approach was selected because of its strength in accommodating missing data and its ability to incorporate random effects into analyses. In these analyses, the dependent variable is the PHQ-9 score, and the independent variables are assignment (treatment condition, wait-list condition) and time [preassessment (T1), each session assessment (T2-T7), post-assessment (T8), and follow-up assessment (T9)], with interaction of the assignment and time as fixed-effect variables and participants as a random-effects variable. Secondary outcomes (outcome measures, process measures, and evaluation of the program) will be analyzed in the same way as the primary outcome. Subgroup analyses are not planned. For all analyses, *P*<.05 will be inferred as statistically significant. Up-to-date versions of R software (R Foundation for Statistical Computing, Vienna, Austria) will be used to analyze the quantitative data.

In the satisfaction/acceptability measure, free comments will be analyzed using thematic analysis.

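### The article gives conflicting primary outcomes: presence of depressive symptoms at 1-month follow-up in one place, PHQ-9 score over nine occasions with no named primary contrast elsewhere

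*Protocol article*

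**What the plan says.** The protocol article describes the primary outcome in several places.

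- **Abstract, Methods:** "The primary outcome is the reduction of depressive symptoms (using Patient Health Questionnaires-9) measured at baseline and weekly", followed by a post-intervention and a 1-month assessment.
- **Sample Size:** a standardised effect of 0.60 on PHQ-9 reduction, two-tailed alpha .05 and power 0.80, giving 90 participants, raised to 100 for 10% dropout.
- **Measures:** PHQ-9 at T1 (baseline), T2-T7 (weekly), T8 (post-assessment) and T9 (1-month follow-up).
- **Primary Outcome Measure:** "The primary outcome measure is the Japanese version of PHQ-9". It is described as nine items, with higher scores meaning more severe symptoms.
- **Statistical Analyses:** "the dependent variable is the PHQ-9 score". The model has assignment and time (all nine occasions), "with interaction of the assignment and time as fixed-effect variables and participants as a random-effects variable". P<.05 applies to every analysis.
- **Results:** "The primary outcome is the presence of depressive symptoms at 1-month follow-up". No instrument, cut-off or test accompanies this sentence.

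No section reconciles the last statement with the others.

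**The concern.** A superiority trial with one primary hypothesis needs one primary variable, one time and one comparison. Here the Results section points to T9 alone, while the other sections point to all occasions. The analysis section does not settle the matter, because a group-by-time interaction over nine occasions leaves open which contrast decides the trial.

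At stake is what the trial may conclude. A benefit that is clear after the programme but fades over the following month would be a failure under the Results wording, yet could be reported as a success from the mixed model. A late benefit could be treated the opposite way. If *presence* is meant literally, the planned linear model and the standardised mean difference behind the sample size also do not apply to it.

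The Results section reports that 60 participants had given baseline data and 24 had started the intervention, so the definition should be settled soon.

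**Working it through.** **1. Statements side by side**

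| Section | Variable | Time |
|---|---|---|
| Abstract | PHQ-9, reduction | baseline, weekly, post, 1 month |
| Sample Size | PHQ-9, reduction (d = 0.60) | not stated |
| Measures | PHQ-9 | T1-T9 |
| Statistical Analyses | PHQ-9 score | T1-T9, no primary contrast |
| Results | *presence* of symptoms, no cut-off | T9 only |

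The last row differs from the others in variable, and from every row that states a time in timing.

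**2. The plan's own figure**

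Inputs from Sample Size and Randomization: d = 0.60, two-sided alpha .05, power 0.80, 1:1 allocation.

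- Normal approximation: n per arm = 2(1.960 + 0.842)² / 0.60² = 43.6, so 44 per arm and 88 in total.
- t-test: 44.59, so 45 per arm and 90 in total. This matches the stated figure.
- Dropout: 90 / 0.90 = 100, as stated.
- Power at 45 per arm: 0.60 × √(45/2) = 2.846, and Φ(2.846 − 1.960) = 0.812. The t-test gives 0.804.

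So 90 is the size for one two-group comparison of means. No time point enters the calculation. It serves a PHQ-9 comparison at T8 or at T9 equally well, provided that 0.60 is expressed in SDs of the quantity compared.

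**3. It was not derived for the nine-occasion interaction test**

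The documents give no correlations or trajectory, so these are assumptions: 45 per arm, a random-intercept model, and a group difference rising linearly from 0 to 0.60 SD, either by T9 or by T8 and then held. The noncentrality is (45/2) × Σ(dₜ − d̄)² / (1 − ρ), on 8 degrees of freedom. The sum is 0.3375 (rise to T9) or 0.3886 (rise to T8, then held).

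| Within-person correlation ρ | Power of 8-df interaction test |
|---|---|
| 0.3 | 63% to 70% |
| 0.5 | 80% to 86% |
| 0.7 | 97% to 99% |

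If correlation decays with time (0.8 to 0.9 between adjacent visits), an 8-df test has about 29% to 47%. The stated 80% is therefore not a property of that test; it belongs to a single contrast.

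**4. How much the choice of time point can matter**

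As an illustration, suppose the difference is 0.60 SD at T8 and half of that, 0.30 SD, at T9. Power at T8 is 0.812 as above. At T9 it is Φ(0.30 × 4.743 − 1.960) = Φ(−0.537) = 0.30. The same trial would probably succeed on one choice and fail on the other.

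**5. Only if *presence* means a yes/no endpoint**

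The documents give no cut-off or prevalence. Assume a normal score shifted by 0.60 SD and a control prevalence p_C at T9. Then p_T = Φ(Φ⁻¹(p_C) − 0.60). With p̄ the mean of p_C and p_T:

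power = Φ{[(p_C − p_T)√n − 1.960√(2p̄(1−p̄))] / √(p_C(1−p_C) + p_T(1−p_T))}

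For p_C = 0.50: p_T = 0.274 and the difference is 0.226. Then (0.226 × 6.708 − 1.960 × 0.689) / 0.670 ≈ 0.25, so power is 0.597.

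| p_C | p_T | Power, 45 per arm | n per arm for 80% |
|---|---|---|---|
| 0.30 | 0.130 | 0.499 | 92 |
| 0.40 | 0.197 | 0.560 | 79 |
| 0.50 | 0.274 | 0.597 | 72 |
| 0.60 | 0.364 | 0.612 | 70 |
| 0.70 | 0.470 | 0.604 | 71 |
| 0.80 | 0.595 | 0.562 | 78 |

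**The case against.** The best defence is that *presence* is loose wording for symptom level. Every section that sets out how the trial works uses the PHQ-9 as a score or a reduction, only the score has a described analysis, and the stray sentence comes without instrument, cut-off or test. The same Results section is loose elsewhere: it dates ethics approval to September 2019, whereas Ethics lists three approvals in 2018. This largely answers the question of variable type, but not that of timing. Even read as severity, the sentence fixes T9 as the primary occasion, which no other section does, and the model names no alternative.

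Four stronger readings are tempting and not supported.

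- A reader might infer that the stated 80% power fits only the score over T1-T9. It does not: it is a single-contrast calculation, valid at T9 as much as at T8, and was not derived for the nine-occasion model.
- A reader might infer that the trial is underpowered. That follows only if a binary endpoint was really meant.
- A reader might infer a false-positive risk near 10% from two primary outcomes. No section plans to test both, and 1 − 0.95² = 0.0975 is the figure for independent tests, which these would not be.
- A reader might take the Study Design statement on post-intervention assessment to make T8 primary. It concerns visit timing only. T9 is the only single time point that the article attaches to the primary outcome.

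**Conclusion.** The concern holds as an unreconciled conflict in the definition of the primary outcome. The conflict on timing is firm: T9 alone against all occasions with no primary contrast. The conflict on variable type holds on a literal reading but may be a slip of wording.

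The practical consequence is freedom over which contrast decides the trial. Under the assumed halving of the effect between T8 and T9, the chance of a significant result is about 81% at one visit and 30% at the other.

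The sample size of 90 (100 with dropout) stands for any single between-arm PHQ-9 mean contrast at d = 0.60. The fall to about 50% to 61% power, with 70 to 92 per arm needed for 80%, is conditional on an intended yes/no endpoint, a 0.60 SD normal shift and a control prevalence of 30% to 80%. None of these is stated in the article.

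This should be corrected before outcome data are examined, because it determines what the trial can conclude.

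**What to change.** State one primary endpoint throughout: the between-arm difference in PHQ-9 total score at one named time point, estimated as that contrast from the linear mixed model. Use T9 if the Results sentence reflects the intent, and T8 otherwise. Then:

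- say in Sample Size that the 90 evaluable participants refer to that contrast, and that 0.60 is in its SD units;
- reword the Abstract, Statistical Analyses and Results sections to match;
- remove *presence of symptoms* as a primary outcome, or keep it as a secondary outcome with a stated PHQ-9 cut-off and a binary analysis;
- check that the registry entry agrees; it is not available here, so whether it needs correction is unknown.

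Do this, with a dated record, before outcome data are examined. The cost is wording only, with no extra participants or visits. The price is that the remaining time points become secondary.

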## Discussion

SPARX is a game-based intervention that was developed to deliver CBT for adolescents with depressive symptoms [22,27]. This program has been demonstrated to be effective for high school students with mild-to-moderate symptoms of depression in New Zealand [26]. The aim of this trial is to investigate the efficacy of the program in Japanese university students using a superiority RCT comparing SPARX with a wait-list control. The findings of this trial are expected to add to evidence of the efficacy of the game-based computerized CBT for young people with depressive symptoms. These results will provide important knowledge for implementation of computerized CBT into existing health support services for university students in the future. However, in this trial, for the purpose of checking SPARX use and being able to answer any questions from a participant, participants in the treatment condition play the SPARX program at a designated university location with one of the researchers present in another room. Therefore, we are not examining the pure effect of SPARX as a self-help tool. This procedure could influence the intervention effect or dropout ratio. In addition, to clarify the benefits and limitations of the effect of SPARX on the university students' depressive symptoms, the effects of SPARX in comparison to an active control will need to be assessed in the future.

## Appendix

Multimedia Appendix 1 CONSORT-eHEALTH checklist (V 1.6.1).

## Abbreviations

Brief COPE: Brief Coping Orientation to Problem Experienced inventory
CBT: cognitive behavioral therapy
CES-D: Center for Epidemiological Studies Depression
DLSS: Daily Life Stress Scale for undergraduates
EuroQol: EuroQol Instrument
LMM: linear mixed model
PHQ-9: Patient Health Questionnaire-9
POMS-2: Profile of Mood States Second Edition
RSS: Ruminative Responses Scale
SPARX: Smart, Positive, Active, Realistic, X-factor thoughts
SWLS: Satisfaction With Life Scale
UMIN: University Hospital Medical Information Network
